## Background

Healthcare-associated infections are ranked by the World Health Organization as one of the top 10 causes of hospital deaths worldwide [1]. In Canada, they are the most common serious complication of hospitalization, affecting 10% of all patients in acute-care hospitals [2] and are the fourth leading cause of death [3]. Healthcare-associated pathogens that can lead to infection are transmitted through direct and indirect contact, droplets, air, and the contaminated hands of healthcare workers (HCWs), the latter being the most common vehicles of transmission in most settings [4]. Microorganisms are known to survive on hands for up to 60 minutes following contact with a patient or contaminated surface. Hand contamination increases with increasing time spend providing direct patient care, in the absence of appropriate hand hygiene [4].

Hand hygiene, defined as the act of washing one’s hands with soap and water or disinfecting them with an antiseptic agent, is the single most successful and cost-effective means of preventing healthcare-associated infections, as well as an effective means of preventing illness in the community that may lead to hospitalization [5-8]. Hand hygiene, before and after all patient or patient environment contact, before aseptic procedure, and/or after bodily fluid exposure, is recommended in all published infection control and public health guidelines and is considered the standard of care for all HCWs [5-10]. Yet many studies document that HCWs’ compliance with hand hygiene recommendations is consistently less than 50% [6,11-15], with compliance among physicians routinely lower than that of other HCWs [16-19]. Locally, at the Ottawa Hospital (proposed for this study), physician hand hygiene compliance rates have increased significantly from 14–17% between 2004–6 to 65–69% in March 2011. In spite of this increase, however, physician compliance continues to lag behind that of most other occupational groups and is below the corporate goal of 80%.

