### Barriers and enablers to physician hand hygiene compliance

Reasons for low hand hygiene compliance by HCWs, and physicians specifically, are poorly understood. Studies investigating HCWs generally have reported a range of barriers, including environmental barriers (*e.g*., lack of access to sinks, difficulty of locating products, empty dispensers, dispensers and time constraints) and personal barriers (*e.g*., attitudinal beliefs, skin irritation from repeated hand washing) [23,24]. Using a behavioural theory approach, Boscart and colleagues explored nurses’ perceived barriers and enablers to hand hygiene practice [25]. Nurses focused on immediate consequences; for example, they identified their personal safety and their families’ safety as a core source of motivation to perform hand hygiene. They also described the importance of individual feedback and self-monitoring in order to increase their performance. With respect to barriers specific to physicians, research is limited. In a recent survey of attitudes towards hand hygiene, physicians reported ‘remembering to perform hand hygiene’ and ‘high workload or feeling too rushed’ as their top barriers to hand hygiene compliance [26]. A second study, which surveyed a variety of HCWs including physicians, found environmental barriers to hand hygiene compliance to be dominant, including lack of soap, broken soap dispensers, and lack of paper towels [27]. Educational gaps in infection control training among physicians also exist [17,18,28,29]; however, strategies effective for improving infection control practices of other HCWs have had significantly less impact on physicians [30,31]. Additional barriers that are specific to physicians that have been identified/postulated include: a perception among physicians that their compliance is much better than it actually is [32,33]; the development of a more cavalier attitude towards infection control as clinical experience increases, with an associated drop in compliance rates [30,34,35]; the lack of positive role models among physicians who are part of a healthcare team [35-37]; and, the local (*e.g*., unit, hospital) culture of patient safety [38].

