### Semi-structured interviews with physician and residents

#### Study population and sampling

Key informants will comprise staff physicians and residents in medicine and surgery at two geographical campuses from a large Canadian urban hospital. Lists of all eligible physicians and residents (divided by campus [n = 2] and specialty [n = 2, medicine and surgery]) will be obtained. From this master list, six new lists will be created for sampling purposes: (1) physicians medicine campus 1, (2) physicians medicine campus 2, (3) physicians surgery campus 1, (4) physicians surgery campus 2, (5) residents medicine, and (6) residents surgery. Residents will not be separated by campus as they work equally across campuses. A quasi-experimental sampling strategy will be used to select key informants from each list. The lists of potential key informants will be arranged in ascending order with respect to the informant’s name (first, last name), with each informant being assigned a number. The first key informant will be chosen at random, and the subsequent key informants will then be selected according to regular intervals, known as periods. A period is determined by dividing the population size (N on the list) by the desired sample size (n that is 5 or 10, depending on the group). The Associate Director of Infection Prevention and Control of the hospital will inform the chosen key informants via email that they have been selected for the study. Key informants who agree to participate will be instructed to contact the study research assistant (SL), at which time they will be provided additional details on the study. If they remain willing to participate after this initial contact, a time will be arranged to conduct the interview. This selection process will be repeated until the required sample size is achieved.

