#### Phase 3: Implementation and pilot of the intervention

We will pilot the theory-based knowledge translation intervention determined in Phase 2 of our work in four patient care units at the same large urban hospital used to collect our data on barriers and enablers. Routine hand hygiene audits collected by the hospital will be used to determine which units are ‘low performing.’ We will randomly select for the pilot, from all ‘low performing’ medical and surgical units, two medical and two surgical units (divided equally between campuses). We will assess effectiveness of the intervention using pre- and post-hand hygiene audits (counts of physicians/residents who washed their hands in accordance with current guidelines), which will be collected by hospital-trained auditors. We will report pre- and post-audit numbers and perform a chi-square test to examine differences between proportions of physicians/residents performing appropriate hand hygiene pre- and post- intervention if there is sufficient sample size (*i.e*., sufficient numbers of physicians/residents audited on each unit). An important element of our evaluation in Phase 3 will be a process evaluation to understand what aspects of the intervention did and did not work. The process evaluation will involve interviews with clinicians (*e.g*., physicians, residents, nurses) on the pilot units as well with hand hygiene experts across the hospital. We will conduct interviews with up to five residents and staff physicians per piloted unit. In the focus group, we will target six to eight hand hygiene experts [60]. We will follow the same process for conducting the focus groups as previously outlined. All process interviews and focus groups will be analyzed using thematic content analysis.

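### The Phase 3 audit comparison takes staff physicians and residents together, so a change in the staff/resident mix between audits can move the result by a modest amount with no change in behaviour

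*Protocol article*

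**What the plan says.** The Phase 3 section (Implementation and pilot of the intervention) places the intervention on four units, two medical and two surgical, drawn at random from units with poor audit results and split evenly between campuses. Its purpose is explicit: "We will assess effectiveness of the intervention using pre- and post-hand hygiene audits". The measure is "counts of physicians/residents who washed their hands in accordance with current guidelines", and the team will "perform a chi-square test to examine differences between proportions of physicians/residents performing appropriate hand hygiene pre- and post- intervention". The only condition on the test is "sufficient numbers of physicians/residents audited on each unit". No split or adjustment by role is stated, and no comparison units are named.

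Three other places bear on this:

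- Study population and sampling (Phase 1): "Residents will not be separated by campus as they work equally across campuses".
- Barriers and enablers to physician hand hygiene compliance: among barriers described as identified or postulated for physicians is "the development of a more cavalier attitude towards infection control as clinical experience increases, with an associated drop in compliance rates". No size is given.
- Generating specific beliefs (Phase 1): beliefs are derived separately for staff and residents within each specialty.

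The Background gives the local scale: "physician hand hygiene compliance rates have increased significantly from 14–17% between 2004–6 to 65–69% in March 2011". That level "is below the corporate goal of 80"%.

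**The concern.** A combined proportion depends on how each group behaves and on how large each group is among those audited. If residents and staff comply at different rates, a second audit that happens to catch relatively more residents, or fewer, gives a different figure even if each group behaves exactly as before.

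The protocol itself supplies grounds for taking this seriously. It cites a fall in compliance with experience, it describes residents and staff as differing in experience when it justifies the interview sample, and it keeps the two roles apart in Phase 1. The one quantitative outcome of Phase 3 names them together.

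If the listed direction holds, a larger resident share at the post audit would look like improvement and a smaller one would hide it. The result is meant to guide refinement of the intervention before a multi-site cluster randomised trial, so a spurious few points, or a real change seen in only one role, would be carried forward unnoticed.

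**Working it through.** The article states no sample size, power or significance level for Phase 3, so there is no figure of its own to reproduce. The check asks how far mix alone could move the result.

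**Formula.** Let r be the resident share of audited observations, and p_R and p_S the compliance of residents and staff. The combined proportion is

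P = r·p_R + (1 − r)·p_S.

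If p_R and p_S stay fixed and only r changes, then

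change in P = (change in r) × (p_R − p_S).

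**Inputs from the document.** Local physician compliance is 65–69% (March 2011, hospital-wide, not split by role) and the goal is 80%. The distance to the goal is 80 − 69 = 11 to 80 − 65 = 15 points. Pilot units are chosen for poor performance, so their own distance may be larger.

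**Inputs assumed.** The resident share, its change between audits, and the compliance gap are not in the document. Ranges are shown instead.

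| Change in resident share | Gap 5 points | Gap 10 points | Gap 20 points |
|---|---|---|---|
| 10 points | 0.5 | 1 | 2 |
| 20 points | 1 | 2 | 4 |
| 40 points | 2 | 4 | 8 |

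Entries are the spurious change in P, in percentage points; for example, 0.20 × 20 = 4.

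**Against the distance to the goal.** For a 20-point change in mix, the artefact is between 1/15 (about 7%) and 4/11 (about 36%) of that distance. Even the extreme cell, 8 points, falls short of 11.

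**Effect on the test.** Assume a two-sided 5% level, independent observations, equal numbers in each period, and compliance centred on 67% (the midpoint of 65–69%). The chance of rejecting in the direction of the shift, from mix alone, is then as follows; without any shift it is 2.5%.

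| Spurious shift | 100 observations per period | 400 observations per period |
|---|---|---|
| 1 point | 3.5% | 4.9% |
| 2 points | 4.8% | 8.7% |
| 4 points | 8.7% | 22.4% |
| 8 points | 22.4% | 67.3% |

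For scale, about 138 independent observations per period would detect a change from 65% to 80%, and about 246 a change from 69% to 80% (80% power, assumed). At 100 per period the distortion is modest unless the shift is extreme; it grows with the number of audits.

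**What stratification does.** Standardised to the pre-period share, the change is r_pre × (change in p_R) + (1 − r_pre) × (change in p_S). This is zero when neither group changes, whatever happens to the mix.

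**The case against.** The strongest reply is that the article names who is audited and does not rule out a breakdown by role. Role tables are the kind of detail an article may leave to a fuller document, and the team already separates the roles in Phase 1. That stands in part: pooling is the natural reading of the stated test, but not the only possible one. What the article does fix is an effectiveness test on the two roles named together.

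The reply also rightly limits how far the point can be taken. A reader might infer more in four ways, none of which the document supports.

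- *That residents are known to leave the pilot units between audits.* The remark about campuses explains how interview lists were built. It gives no rotation schedule and says nothing about individual units. Turnover is a possibility, not a stated fact.
- *That a quarter to a half of the effect is lost through unexposed newcomers.* This would follow from effect × (1 − r·t), with r = 0.5 and the replaced share of residents t between 0.5 and 1, if newcomers gained nothing. The intervention is still to be designed in Phase 2, so whether newcomers would miss it cannot be known and the loss cannot be sized.
- *That auditing different people at the two times is a fault.* For an intervention placed on units, two cross-sections are a usual design, and an ordinary chi-square test assumes independent samples.
- *That staff physicians should be the main reading.* Residents are part of the target group and supply 20 of the 40 planned interviews.

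Finally, this is a pilot, and its process interviews with residents and staff on each unit may reveal some of these problems. That lowers the weight of the point. It does not remove the mix from the stated test.

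**Conclusion.** The point holds in a limited form. The stated comparison has no protection against a change in the staff/resident mix, and the protocol's own text gives reason to think the two roles may differ. For an assumed 20-point change in resident share and a 5 to 20-point gap, the bias is 1 to 4 points; across the wider range shown it is 0.5 to 8 points. Both inputs are assumptions, and the experience gradient is offered as identified or postulated, without a size.

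It would be wrong to conclude that mix is why the change cannot be attributed to the intervention. Attribution fails mainly because there are no concurrent comparison units, because units are selected for poor audit results and may drift back towards their usual level, and because local compliance had already been rising. Handling role properly repairs none of these. The mix is one additional, bounded and separately fixable threat, so this is a low-cost improvement rather than a major flaw.

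**What to change.** 1. Record staff or resident status for each audited observation, before and after.
2. Report the pre and post proportions, and their change, separately for staff physicians and residents.
3. Base any combined comparison on a role-stratified test, for example Mantel-Haenszel, or on proportions standardised to the pre-period mix.
4. Show the resident share in each period, so that a reader can see whether the mix moved.

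The cost is one extra field on the audit record and a somewhat longer table. The drawback is smaller counts per stratum, in a pilot that already makes its test conditional on enough people being audited. Where counts are thin, the role-specific figures can be given descriptively.

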## Methods

In this study, we define hand hygiene as: any action of hand cleaning that removes visible soil and removes and kills any microorganisms on the hands. We propose to use state of the art approaches from knowledge translation science to, first, identify key factors that act as barriers and enablers to best hand hygiene practice by physicians and then develop and pilot a knowledge translation intervention focused on improving hand hygiene compliance by physicians that is based on the identified barriers and enablers.

The study will be subdivided into three phases to be executed over one year:

Phase 1: identification of barriers and enablers to hand hygiene compliance by physicians. This will include: key informant interviews with physicians and residents; nonparticipant observation of physician/resident hand hygiene behaviours during regular hospital hand hygiene audit sessions; and focus groups with hand hygiene experts (this Phase is equivalent to Phase 0 in MRC framework).

Phase 2: intervention mapping to develop a theory-based knowledge translation intervention to improve physician hand hygiene compliance (this Phase is equivalent to Phase 1 in MRC framework).

Phase 3: implementation and pilot of the knowledge translation intervention (this Phase is equivalent to Phase 2 in MRC framework).

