A limitation to this study will be measurement of the target behaviour (*i.e*., measurement of hand hygiene compliance). There are three main methods for measuring hand hygiene performance, each of which has advantages and disadvantages: directly observing, measuring product use, and self-report. Direct observation of hand hygiene behavior of HCWs chosen for this study is considered the ‘gold standard’ of measurement methods. It allows you to see which hand hygiene products are used, the thoroughness of cleansing, and importantly, whether the staff is performing hand hygiene whenever there is an opportunity to do so. This method also allows observers to give prompt feedback about whether improvement is needed. On the other hand, direct observation is also labor intensive and expensive, requiring the careful selection and training of those who will observe and record data. It can also influence the behavior of those who know they are being observed, which is a potential bias in our study. The success of this method depends on the accurate calculation of adherence rates, the careful training of data collectors, and the data collectors’ uses of clear, easy-to-understand forms. Therefore, in an attempt to limit bias, we will use hospital-trained auditors.

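### The Phase 3 effectiveness outcome is a proportion of persons tested by a plain chi-square, although hand hygiene is due at several moments per patient contact and one physician can be observed repeatedly.

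*Protocol article*

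**What the plan says.** The section Phase 3: Implementation and pilot of the intervention uses persons as the unit three times.

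- The outcome is "counts of physicians/residents who washed their hands in accordance with current guidelines".
- The chi-square test examines "differences between proportions of physicians/residents performing appropriate hand hygiene pre- and post- intervention".
- The test is run only with enough data, explained as "sufficient numbers of physicians/residents audited on each unit".

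Other sections describe a behaviour that recurs within a contact. The Background says hand hygiene is recommended "before and after all patient or patient environment contact, before aseptic procedure, and/or after bodily fluid exposure". The Discussion lists, among the advantages of direct observation, that it shows "whether the staff is performing hand hygiene whenever there is an opportunity to do so".

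The article gives no number of opportunities observed per physician, no rule for a physician seen more than once, and no sample size, significance level or power for Phase 3.

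**The concern.** One patient contact creates at least two moments for hand hygiene, before and after. A physician who cleans before but not after is neither plainly compliant nor plainly non-compliant, so a count of compliant persons needs a further rule. Under any such rule based on all or any of the moments seen, the result depends on how many moments the auditor watched. If that number differs between the two audit periods, the outcome can move with no change in behaviour.

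The alternative reading is that each audit record is one opportunity and that *physicians/residents* is loose wording. The dependence on the number watched then disappears, but several records can come from one physician, and a plain chi-square treats them as independent.

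The audits are the only quantitative effectiveness measure described for the pilot. The Discussion says the piloted intervention will be refined for a multi-site cluster randomised trial, so a poorly chosen unit could carry forward.

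**Working it through.** The plan states no Phase 3 figure that could be reproduced. What follows is an illustration under stated assumptions.

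**Inputs**

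- Compliance per opportunity, p = 0.67. This is the midpoint of the latest local figure in the Background ("physician hand hygiene compliance rates have increased significantly from 14–17% between 2004–6 to 65–69% in March 2011"), taken here as per opportunity. The article does not state its denominator.
- Opportunities watched per physician, m = 1, 2 or 3 (assumed).
- Within-physician correlation, ρ = 0, 0.2 or 0.5 (assumed).
- Physicians per period, n = 50, 100 or 200, with two-sided α = 0.05 (assumed).

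**Step 1: the person-level proportion under two possible rules, ρ = 0**

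All-or-none: P = p^m. At least once: P = 1 − (1 − p)^m.

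| m | All-or-none | At least once |
|---|---|---|
| 1 | 0.670 | 1 − 0.33 = 0.670 |
| 2 | 0.67² = 0.449 | 1 − 0.33² = 0.891 |
| 3 | 0.67³ = 0.301 | 1 − 0.33³ = 0.964 |

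The same behaviour gives 45% or 89% at m = 2, depending on a rule that the article does not state. With p = 0.65 the all-or-none values at m = 2 and 3 are 0.423 and 0.275. With p = 0.69 they are 0.476 and 0.329.

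**Step 2: within-person correlation**

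At m = 2 the all-or-none proportion is p² + ρp(1 − p), with p(1 − p) = 0.67 × 0.33 = 0.2211.

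- ρ = 0: 0.449
- ρ = 0.2: 0.4489 + 0.0442 = 0.493
- ρ = 0.5: 0.4489 + 0.1106 = 0.559

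Against 0.670 at m = 1, the gap shrinks from 22.1 to 17.7 and 11.1 points. It does not vanish.

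**Step 3: can the test mistake this for an effect?**

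Suppose p is unchanged, ρ = 0, the rule is all-or-none, and m goes from 2 before to 3 after. The proportion moves by 0.301 − 0.449 = −14.8 points. The chance of a significant chi-square is about Φ{(|Δ| − 1.96√[2p̄(1 − p̄)/n]) / √[(p₁(1 − p₁) + p₂(1 − p₂))/n]}, where p̄ is the mean of the two proportions. At n = 100 this is Φ{(0.1481 − 0.1342)/0.0677} = Φ(0.21) = 58%. It is 33% at n = 50 and 87% at n = 200.

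**Step 4: if the records are opportunities**

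The person and opportunity proportions then coincide, and the remaining problem is the standard error.

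- Different physicians in the two periods, m records each per period: the variance is multiplied by 1 + (m − 1)ρ. At m = 2, ρ = 0.2 this is 1.2, so the true standard error is √1.2 = 1.10 times the one used. At m = 3, ρ = 0.5 it is 2.0, a ratio of 1.41.
- The same physicians in both periods, with equal correlation throughout: the covariance between periods enters, and the factor for the difference is 1 + (m − 1)ρ − mρ = 1 − ρ. At ρ = 0.2 the ratio is √0.8 = 0.89, so the chi-square is too cautious.

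The standard error is therefore wrong in either case. The direction depends on how far the same physicians appear in both periods.

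**The case against.** The strongest reply is that each record may be one physician at one opportunity. If every physician is also observed only once, m = 1, the two proportions are equal and nothing is distorted. That is correct, but the article does not say so. Repeats are plausible: there are only four units, audited before and after, and residents are said to work across both campuses. If physicians do recur, either the denominator is misnamed or the independence behind the test fails.

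A second reply is that scoring rules belong in a fuller protocol or audit manual, and that a conditional test in a four-unit pilot settles nothing. A missing scoring rule would indeed be no finding in an article. The point concerns what is stated: a unit and a test that suit the behaviour badly. The pilot setting limits the consequences but does not make the unit right.

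Several stronger readings are tempting and are not supported.

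- *Compliance is defined per opportunity elsewhere.* It is not. The Background lists guideline moments and the Discussion describes what observation can show. Neither sets a numerator and denominator, so there is no formal contradiction.
- *The outcome does not match the local 65–69% or the hospital's 80% target.* Neither figure has a stated denominator, and Phase 3 does not compare the pilot with them. Comparability is unknown.
- *Washed excludes hand rub.* The phrase is tied to current guidelines, the next sentence speaks of appropriate hand hygiene, and the Background counts washing one's "hands with soap and water or disinfecting them with an antiseptic agent". This is a wording correction only.
- *Auditors must verify the Methods definition,* "any action of hand cleaning that removes visible soil and removes and kills any microorganisms on the hands". That is a conceptual definition for the whole study. Phase 3 applies accordance with guidelines, which an auditor can observe.

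**Conclusion.** The point holds in a limited form. The stated unit (persons) and test (plain chi-square) do not suit a behaviour due several times per contact and observable repeatedly in the same physician. A person-level proportion is undefined for partial compliance and can depend on observation intensity: 67%, 45% and 30% at 1, 2 and 3 opportunities, given p = 0.67, independence and an all-or-none rule. Under correlation the shift is smaller, and with one observation per physician it is zero. If the records are opportunities, the proportion is sound but its standard error is not.

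A reader might infer that a bias of about 15 points is to be expected. The documents do not support that. The figure needs m to move from 2 to 3 between periods, independence and an all-or-none rule, and the article states none of these. It shows what could happen and does not predict the pilot's result. The plan should be changed, but nothing here invalidates the pilot.

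**What to change.** In the Phase 3 section:

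1. Define the outcome as opportunities at which guideline-accepted hand hygiene was performed (soap and water or rub), divided by opportunities observed, per unit and period. Take the opportunities from the guideline moments listed in the Background.
2. Replace the plain chi-square with an analysis that allows for clustering by physician, or by audit session if the audits do not identify physicians. Where physicians are identified, the analysis should also use the fact that some appear in both periods.
3. State the sample-size condition in opportunities, and in physicians or sessions.
4. Replace *washed their hands* with *performed hand hygiene*, as a wording correction.

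The cost is rewording and a little more analysis, provided the audit forms already record opportunities. That is assumed and should be confirmed with the hospital; otherwise the form must change before the first audit. Intervals will usually be somewhat wider: about 10% at m = 2, ρ = 0.2, and more with stronger correlation or more repeats. They may be narrower where the same physicians are seen in both periods.

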## Discussion

Addressing physician behaviour is especially important given the role model and leadership roles that physicians play in healthcare settings. A better understanding of the rationale for specific physician behaviours related to hand hygiene will provide a more comprehensive framework on which to develop interventions that have a better than random chance of being successful in effecting change in this group. This can be achieved through the application of a behavioural theory approach such as that which will be applied in this study. The study presented in this protocol is based on the TDF that is derived from theories of behaviour [44]. Conducting semi-structured interviews (based on the TDF) to identify important theoretical domains to behaviour change is an approach that has rarely been used before, and to our knowledge has never been used with respect to physicians’ use of hand hygiene practice.

This study corresponds to specific aspects of the UK’s MRC framework for developing complex interventions [39,40], namely, phases 0 (problem and contextual assessment and development of the theoretical basis for an intervention), 1 (definition of components of the intervention), and 2 (exploratory studies to develop further the intervention and plan a definitive evaluative study). It is now argued that these phases should be considered as part of a larger iterative activity (as will be done in this study), rather than as sequential studies [40]. It is also believed that insights gained during these early phases of intervention development and implementation can make valuable contributions to the science of knowledge translation [40]. Upon completion of this study, we will know the barriers and enablers to physician hand hygiene compliance and have developed and piloted a theory-based knowledge translation intervention that addresses these barriers/enablers. In the future, we plan to refine the piloted intervention so it can be tested in a multi-site cluster randomized controlled trial.

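### The Phase 3 chi-square test is not tied to the four units combined or to each unit, and an unstratified test would let a change in audit mix look like an intervention effect

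*Protocol article*

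**What the plan says.** The protocol article, under Phase 3: Implementation and pilot of the intervention, draws the pilot from low-performing wards: "two medical and two surgical units (divided equally between campuses"). The purpose of the audit data is stated as "We will assess effectiveness of the intervention using pre- and post-hand hygiene audits". The analysis is to report the audit numbers and "perform a chi-square test to examine differences between proportions of physicians/residents performing appropriate hand hygiene pre- and post- intervention". That test is to be run only "if there is sufficient sample size (*i.e*., sufficient numbers of physicians/residents audited on each unit").

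The section does not say whether the table is formed over all four units or separately in each. It does not say what happens if only some units have enough audits, and it does not fix how many audits each unit contributes in either period. The Discussion gives the next step: "we plan to refine the piloted intervention so it can be tested in a multi-site cluster randomized controlled trial".

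**The concern.** The singular test suggests one overall comparison. The per-unit condition leaves room for unit-level comparisons. The choice matters because the two forms answer different questions, can disagree on the same data, and need very different audit numbers to count as sufficient.

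The overall form has a weakness of its own. A plain 2×2 table of period by compliance discards unit. The pilot deliberately spans medicine and surgery on two campuses, so unit rates may well differ. If one unit supplies a larger share of the audits after the intervention than before, the crude rate moves even when every unit stays the same. That movement would be read as effectiveness, or would mask it, and would be carried into the case for the later cluster randomised trial.

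**Working it through.** The article gives no alpha, power, effect size or audit count for Phase 3, so there is no planned figure to reproduce.

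**Inputs.** From the document: four units, a binary outcome, two periods, and hospital-wide physician compliance of "65–69% in March 2011" (Background) as context. Assumed: two-sided 0.05 per test, independent audits, 50 audits per unit per period for the power figures, and the unit rates and counts shown below.

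**1. Audit mix in an unstratified table.** The crude rate is the sum of (audits × unit rate) divided by total audits. Unit rates are held at 45/55/65/70% in both periods.

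- Before, with 60/50/50/40 audits: (27 + 27.5 + 32.5 + 28)/200 = 115/200 = 57.5%.
- After, with 40/50/50/60 audits: (18 + 27.5 + 32.5 + 42)/200 = 120/200 = 60.0%.

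The apparent gain is 2.5 points with no change in any unit. Equivalently, a tenth of all audits moves from the first unit to the fourth, so the shift is 0.10 × (70 − 45) = 2.5 points. If those two units differed by half as much, it would be 0.10 × 12.5 = 1.25 points. In simulation, the mild shift above raises the false-positive rate of the crude test from 5% to about 7.4%. A unit-stratified risk difference is a weighted average of the within-unit differences. Here each of these is zero, so it is zero.

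**2. Power of unit tests against one overall test.** Normal approximation: power = Φ{[δ − 1.96·√(2p̄(1−p̄)/n)] / √[(p₁(1−p₁) + p₂(1−p₂))/n]}, with p₁ = 0.60, p₂ = 0.70, δ = 0.10 and p̄ = 0.65.

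- One unit, n = 50 per period: Φ[(0.10 − 0.187)/0.0949] = Φ(−0.917) = 18%.
- Four units combined, n = 200 per period: Φ[(0.10 − 0.0935)/0.0474] = Φ(0.137) = 55.5% (56% in simulation).

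**3. False positives with four unit tests.** 1 − 0.95⁴ = 18.5% for independent tests.

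**4. The two forms can disagree.** With 30/50 compliant before in every unit:

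| After, by unit (of 50) | Unit p-values | Overall p-value |
|---|---|---|
| 36, 36, 36, 36 | 0.21 in each | 0.011 |
| 40, 28, 28, 30 | 0.029, 0.69, 0.69, 1.0 | 0.54 |

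For a true rise from 60% to 70% in every unit, the overall test is significant with no significant unit in 12.6% of simulated pilots. At least one unit is significant with the overall test not significant in 11.7%.

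**5. What counts as sufficient.** For 80% power to detect 60% to 80%: n = [1.96·√(2·0.7·0.3) + 0.8416·√(0.24 + 0.16)]²/0.20² ≈ 81.2, so 82 audits per period. That is 82 in total for one overall test, but 82 in each unit, 4 × 82 = 328 in total, for unit tests.

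**The case against.** A reader might infer that the text contradicts itself by announcing a pooled test with a unit-level condition. It does not. It never describes the test as pooled, and one overall test run only when every unit is adequately audited is a coherent reading. It would also ensure that all four units are represented. What remains is an ambiguity.

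A reader might also infer that the plan allows an overall test and four unit tests together, each at full alpha. The document announces no unit tests, no combination of tests and no alpha. The 18.5% therefore describes one possible reading under an assumed 0.05, and is not the error rate of the stated plan. An alpha or multiplicity rule may stand in a fuller document, and its absence from an article is not a finding.

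The illustration of audit mix can be pushed too far. A complete reversal of audit volumes, from 80/60/40/20 to 20/40/60/80, moves the crude rate from 54.5% to 63.0% and gives a false-positive rate of about 40%, but nothing in the documents suggests such a reversal. The assumed spread may also be generous: all pilot units are chosen as low performing, yet a 70% unit lies just above the hospital-wide range.

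Finally, the Guiding framework and Methods sections place Phase 3 at an exploratory stage. No decision rule hangs on a p-value, the audit counts will be reported alongside any test, and the process evaluation carries much of the weight. All of this stands and limits the severity. It does not remove the point that the article itself chose a test that ignores unit and left its scope open.

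**Conclusion.** The point holds as an ambiguity combined with a method that is easy to improve. The article does not say whether the pre/post test is over the four units or within each. An unstratified overall test is exposed to changes in audit mix: 2.5 points under a mild assumed shift, in proportion to the spread between units. Unit tests would have about 18% power against 56% combined in the scenario shown, and an 18.5% chance of at least one false positive among four.

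These figures rest on assumed unit rates, audit counts, a two-sided 0.05 and independent audits. None of them is given in the article. The documents do not support a claim of contradiction, of multiple testing that is actually planned, or of a large bias. Severity is minor to moderate.

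**What to change.** Replace the chi-square sentence with one named contrast: the change in compliance from before to after across all four pilot units, stratified by unit. A Mantel-Haenszel common risk difference with its confidence interval would serve, as would a model with unit as a fixed effect. Apply the sample-size condition to this combined contrast. Report the four unit-level changes descriptively, without significance tests.

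The cost is one or two sentences. No new data are needed: the audits are already used to classify units as low performing, so the unit of each audit is known. The loss is that no significance claim can be made for an individual unit. Stratifying by unit does not deal with repeated audits of the same person, so the independence assumption should be stated with the result.
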